### Planned interventions: control and intervention groups

In the clinical pilot, participants will be randomly allocated into two groups: Participants in the control group will receive the usual care provided at the medical center, while participants in the intervention group will be provided with a mobile app that allows them to receive tailored motivational messages in addition to the usual care. Similarly, participants in the public pilot (those who download the app but do not visit the medical center) will also be randomly allocated into two groups. Those in the control group will receive basic tailored messages without prioritization (the system sends a random message from a list of messages whose contents fit the user profile). Users in the intervention group will receive messages that are more specifically tailored to them (the message to be sent will be determined by its usefulness as reported by others with a similar user profile).

### Data management and quality assurance

Participants’ clinical data will be input by physicians into the Realsun, which is a Taiwanese EHR system [37], as is routinely done in usual care. To ensure confidentiality, the data will only be accessible by the physicians and researchers involved this project, and the Taipei Medical University Hospital will classify the data as secrets based on legal regulations.

Participant data related to mobile phone activity (including profile details participants of the public pilot, and their registered physical activity time) will be automatically stored in a secure password-protected electronic database located at the ICHIT department of the Taipei Medical University that uses PostgreSQL and is accessible only to researchers involved in this study. Additionally, participants who drop out of the study will be registered along with their reasons for doing so.

The results of this study will be published in peer-reviewed scientific journals and presented at national and international conferences. Moreover, anonymized datasets from the study will be available via a data management system and thereby accessible to third-party researchers. The system will be based on CKAN [38], an open-source data portal platform. It will be possible to use, search, share, and publish these data.

We will assure the quality of the data entry process by checking use cases during the app’s testing period: the data that are stored in the database will be evaluated to be the same that is expected values after the use case. If it were not the correct, the system would be debugged until it is fixed. Furthermore, random checks will be conducted throughout the duration of the study at a minimum frequency of once per month to ensure that the data are being stored correctly.

Only participants who meet the study’s eligibility criteria, which include signing the informed consent after a full explanation of its consequences, will be enrolled in the clinical pilot. Only participants who accept the terms and services of the app will be enrolled in the public pilot. Data will be kept for 5 years after the research is completed after which all electronic and paper copies will be destroyed.

All consultations will take place at the smoking cessation units at the Wellcome Clinic and Taipei Medical University Hospital. The data analysis will be done at the Taipei Medical University (Taiwan), and the University of Seville (Spain). The Data Monitoring Committee will be formed by researchers of these two institutions with total independence from the sponsors and with no competing interests.

No harm nor additional adverse events from regular smoking cessation care are expected as part of the clinical trials. No harm nor any adverse events are expected as part of the public trial.

The status of the trials is reported to the SmokeFreeBrain Project Consortium. The Data Monitoring Committee members are part of this consortium. It is the consortium, led by its coordinator, who may decide to terminate the trials if the monthly interim analysis show deviations from the expected plan.

### Procedure for generating texts

The motivational messages include a wide range of topics, such as physical activity recommendations, diet tips, reminders about the benefits of being a non-smoker, advice for coping with temptation, little known facts about smoking, suggestions to avoid relapses, how to develop skills required to quit effectively, smoking-related social influences, planning actions to change, quitting smoking self-efficacy expectations, and attitudes towards smoking cessation. The recommender system uses de Vries’s I-Change (or Integrated) model [29–31] to tailor messages to users and guide them toward an effective behavioral change.

The messages are designed to cover the different behavioral-change factors – determinants that the I-Change model suggests we should address in order to foster a behavior change. This process consists of two steps. The first one is checking the users’ profile, which was previously answered by the own user through a series of in-app questionnaires. These questions depict the I-Change users’ profile, providing information about their behavioral determinants (attitudes, social support, skills, self-efficacy, intentions, action planning, etc.). After that information is known, the system iterates over a set of 228 different messages that can be sent to the user. Each message is categorized in one of the 131 to different profiles types created based on the I-Change model. For instance, a message could be targeted to young female users with low social support to quit smoking, while other could be targeted to elder male users which have low self-efficacy levels to quit. Then, the system discards those messages which are incompatible with the user we are going to send the message to – for instance, messages targeted to pregnant women if the user is a male –. Finally, the system selects the message which has the highest usefulness rating by other users. The usefulness rating is recorded every time a user receives a message in their phone with a five-star scale.

### Randomization

In the clinical pilot, randomization will be done with computer-generated random numbers in the website www.randomizer.org. In the public pilot, the randomization process is handled by the server using the JavaScript random method called Math.Random().

### Methods to protect against other sources of bias

The clinical pilot component of this study is designed to be a single-blinded randomized control trial. Care providers at both medical centers will be instructed to treat patients from both groups equally and they will be responsible for patient allocation. Since they do not have any competing interest, we think it is unlikely they influence any group by the lack of blinding. Conversely, the public pilot will be double-blinded as there is no direct interaction with care providers (Table 1). In both cases, outcome assessors will be blinded although the different variables in the datasets will determine the groups.

To avoid bias in the clinical pilot, non-clinical researchers not involved in providing the intervention will be in charge of assessing the results. In the public pilot, although there are no people directly involved providing the intervention, and there is a low risk of bias in the results assessment, the analysis will be done by the same non-clinical researchers not involved in providing the clinical pilot intervention.

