**Methods:**

Our study will gather data from two sources. The first source is a clinical pilot in which a group of patients from two Taiwanese medical centers will be randomly assigned to either an intervention or a control group. The intervention group will be provided with a mobile app that sends motivational messages selected by a recommender system that takes the user profile (including gender, age, motivations, and social context) and similar users’ opinions. For 6 months, the patients’ smoking activity will be followed up, and confirmed as “smoke-free” by using a test that measures expired carbon monoxide and urinary cotinine levels. The second source will be a public pilot in which Internet users wanting to quit smoking will be able to download the same mobile app as used in the clinical pilot. They will be randomly assigned to a control group that receives basic motivational messages or to an intervention group, that receives personalized messages by the recommender system. For 6 months, patients in the public pilot will be assessed periodically with self-reported questionnaires.

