### Recruitment procedure

The participants in this study can be divided into two groups: those who participate in the clinical pilot and those who take part in the public pilot. Participants in the clinical pilot will be recruited from smoking cessation units at Taipei Wellcome Clinic and the Taipei Medical University Hospital in Taiwan between 1 September 2017 and 31 July 2018. They will be asked by a nurse or researcher, whether they want to be part of the study in the waiting room before their first visit to the smoking cessation unit. They will be handed written information about the reasoning of the study, and further, they have to sign an informed consent to participate (Additional file 2). The public pilot will be open to any smoker who is willing to quit. In both pilots, each participant must own an Android mobile phone, and accept the terms and conditions of the services provided by the 3M4Chan app. The participants for the public pilot will be recruited online among all the Taiwanese population between 1 September 2017 and 31 July 2018. They will be invited to join the study by downloading the app. These invitations will be done with targeted ads on Facebook and Google, as well as with retargeting banners, which have previously been proven to be successful [36]. In addition, posters and informative leaflets will be distributed at the above-mentioned smoking cessation units and at Health Promotion Administration centers in Taiwan to attract candidates in non-digital environments. A total of four posters, 200 leaflets, and 400 business card-sized advertisements will be printed to disseminate information about the app.

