### Inclusion/exclusion criteria

In order to be eligible for the clinical pilot study, each patient has to meet the following inclusion criteria. Participants will be required to be a current smoker aged 20 years or older who owns an Android mobile phone and is able to read Mandarin. Additionally, only those who have smoked at least once per month for the past 2 years and are willing to share information from their medical Electronic Health Record (EHR) with project researchers will be considered. Furthermore, patients will be required to sign an informed consent and agree to be followed up for 6 months.

For the public pilot study, all interested people who download the 3M4Chan app in their Android smartphone, who are aged 20 years or older, and who can read English or Mandarin will be able to join.

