At the fourth consultation, physicians will collect information about smoking-related symptoms, treatment adherence, and possible adverse events. Techniques for avoiding the risk of relapse are reinforced. Data about blood pressure, weight, height, and quality of life (using EQ-5D-5 L, IPAQ, and SF-36 questionnaires as well as a questionnaire assessing the satisfaction about the motivational messages received through the 3M4Chan app) will also be collected. All input clinical data will be checked for correctness by two healthcare professionals to ensure quality.

The public pilot will use the same mobile app as the clinical pilot. No additional materials will be used.

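### Clinical pilot: unblinded care providers are responsible for allocation, and the app withheld from controls is advertised in the units that treat them, with no rule keeping them out of the public pilot

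*Protocol article*

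**What the plan says.** **Allocation.** The Randomization section gives the source of the clinical sequence: "randomization will be done with computer-generated random numbers in the website www.randomizer.org". The section on protection against other sources of bias says of the care providers at both centres that "they will be responsible for patient allocation". It accepts that they are not blinded and answers the risk by noting that they have no competing interest: "we think it is unlikely they influence any group by the lack of blinding".

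**Access to the app.** Clinical controls are to receive usual care without the app. Under Recruitment procedure, to attract public-pilot candidates, "posters and informative leaflets will be distributed at the above-mentioned smoking cessation units". Those are the two units that recruit and treat the clinical pilot. The app is not a different one: "The public pilot will use the same mobile app as the clinical pilot". Public-pilot eligibility covers "all interested people who download the 3M4Chan app in their Android smartphone", subject to age 20 or over and reading English or Mandarin. The section on planned interventions, however, describes public-pilot users as downloaders who do not attend the medical center.

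**Assessment.** The protocol says that "outcome assessors will be blinded although the different variables in the datasets will determine the groups", and gives the analysis to non-clinical researchers who take no part in the intervention.

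**The concern.** Two routes to bias follow from what the protocol states, not from detail that an article may leave out.

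The first is selection. A competing interest is only one reason to steer an allocation. A clinician who believes in the app can time enrolment, or place a motivated patient, with no stake in the result. What prevents this is not knowing the next assignment before the patient is committed. The reason the protocol gives does not address that. Bias of this kind cannot be removed by analysis, and it can go in either direction.

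The second is contamination and overlap. Clinical participants must be at least 20, own an Android phone and read Mandarin, so every clinical control automatically meets the public-pilot criteria. Controls attend the units for the initial consultation and again at 60, 120 and 180 days, where the app may be advertised to them. A control who installs it moves the comparison towards no difference. That control is also randomised a second time and can contribute outcomes to both pilots. Advertising public recruitment to patients of the medical centers conflicts with the description of public users as people who do not go there.

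**Working it through.** **Inputs from the protocol.** Sample size section: expected proportions 0.2 and 0.5, two-sided alpha 0.05, beta 0.2, 45 per arm. Abstract and Table 1: 50 per arm planned.

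**The plan's own figure.** The pooled two-proportion formula is

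n = [1.96·√(2p̄(1−p̄)) + 0.842·√(p₁(1−p₁)+p₂(1−p₂))]² / (p₂−p₁)²

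With p̄ = 0.35 this gives 38.5, so 39 per arm. The continuity-corrected version gives 44.9, so 45 per arm. The stated 45 is reproduced, and the sample size is not in question here.

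**Power formula used below** (uncorrected, n = 50 per arm)

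Power = Φ[(|p₂−p₁| − 1.96·s₀)/s₁], where s₀ = √(2p̄(1−p̄)/n) and s₁ = √((p₁(1−p₁)+p₂(1−p₂))/n)

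At 0.2 versus 0.5: s₀ = 0.0954, s₁ = 0.0906, (0.30 − 0.1870)/0.0906 = 1.248, power 89%. The continuity-corrected version gives 85%.

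**Selection.** Assume no true effect, a control rate of 20%, and an intervention rate raised only by who was placed in that arm. The size of the shift is assumed; the documents give none.

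| Assumed imbalance | Rates | Calculation | False-positive rate |
|---|---|---|---|
| none | 20% v 20% | nominal | 5% |
| 5 points | 20% v 25% | (0.05 − 0.1637)/0.0834 = −1.36 | 8.6%, or 9.2% with the other tail |
| 10 points | 20% v 30% | (0.10 − 0.1697)/0.0860 = −0.81 | 21% |
| 15 points | 20% v 35% | (0.15 − 0.1750)/0.0880 = −0.28 | 39% |

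The placement of the shift matters. Centred on a 20% average, the same imbalances give 9.5%, 24% and 47%. With the continuity correction the rows give about 6%, 15% and 30%, against a nominal rate of about 3% for that conservative test.

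**Contamination.** Let c be the share of controls who install the app (assumed) and k the average share of the full 0.30 effect that they obtain. The control rate becomes 0.20 + 0.30·c·k, compared with 0.50.

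- k = 1: every installer gets the full effect. This is an upper bound.
- k = 0.5: the public pilot randomises installers between basic and advanced messages, half get the advanced ones, and basic messages add nothing (assumed).

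| c | Control rate, k = 0.5 | Power | Control rate, k = 1 | Power |
|---|---|---|---|---|
| 0 | 20.0% | 89% | 20% | 89% |
| 10% | 21.5% | 86% | 23% | 81% |
| 20% | 23.0% | 81% | 26% | 70% |
| 30% | 24.5% | 76% | 29% | 58% |

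If basic messages carry half the effect (k = 0.75, assumed), power is 83/76/67%. With the continuity correction, power starts at 85% and falls to 80/75/69% for k = 0.5 and to 75/62/49% for k = 1.

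**The case against.** **On allocation.** Being responsible for allocation is compatible with opening a concealed assignment after consent, and an article may leave the concealment procedure to the full protocol. A reader might infer that treating staff hold the random list, see the next assignment or pick the arm. The documents do not support that: the numbers are computer-generated and nothing says who keeps them. What stands is narrower. Unblinded staff are named as responsible, and the one safeguard given in writing does not bear on foreknowledge.

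**On size.** A shift of 10 or 15 points from steering alone requires staff who predict quitting well and act on it consistently. No figure in the protocol supports this, so 21% or 39% should not be read as the expected error rate; the low end, about 9%, belongs in the range. Likewise, 81/70/58% gives every installer the full effect, although installers would be randomised to basic or advanced messages. That is a worst case, not an estimate.

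**On overlap.** Four posters, 200 leaflets and 400 cards are few, and posters and leaflets are shared with Health Promotion Administration centers. The description of public users as not attending the medical center shows an intention to keep the pilots apart. It is a description, though, not an eligibility criterion, and advertising in the units works against it.

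**On assessor blinding.** A reader might treat the admission that dataset variables reveal the arm as a major flaw. It adds little. The clinical primary outcome rests on expired carbon monoxide and a positive/negative cotinine test, with discrepancies counted as smoking, so assessors have little to judge. A biochemical outcome limits detection bias, but does nothing about selection or contamination.

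**Conclusion.** The concern holds in limited form. As written, the clinical pilot relies on the disinterest of unblinded staff where it needs protection against foreknowledge. It also advertises the intervention app to its own controls with no rule keeping them out of the public pilot. The possible consequences are selection bias of unknown direction, dilution of the usual-care contrast, and people counted in both pilots.

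The size cannot be derived from the documents. Under the assumptions shown, with 50 per arm and the uncorrected formula, the false-positive rate is about 9–39% for an imbalance of 5 to 15 points above a 20% control rate. Power is 86/81/76% with 10/20/30% of controls installing the app, and 81/70/58% at worst. The protocol does not show that allocation is actually foreseeable or how many controls would install the app, so this is a point that should be fixed, not proof that the comparison is invalid.

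**What to change.** Recruitment is under way, so changes to allocation protect only the patients still to be enrolled.

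- Have the existing study server, or the non-clinical researchers already named, generate and hold the clinical sequence. Release each assignment only after consent and baseline entry, and say so in place of the appeal to absent competing interests.
- Add a question at public-pilot sign-up that excludes clinical-pilot participants, and write this into the eligibility criteria so that they agree with the description of public users.
- Move public-pilot posters and leaflets out of the two recruiting units; keep the Health Promotion Administration centers and the online advertising.
- Ask clinical controls about app use at each visit, and check the two pilots for people enrolled in both. This is also possible for patients already enrolled.

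The cost is some set-up work for the server or staff, one sign-up question, one question per visit, relocation of a few printed items, and slightly fewer leaflet recruits at two sites.

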## Methods

### Design and setting

The primary objective of this study is to assess whether tailored motivational messages supporting smoking cessation—as selected by a health recommender system and delivered by mobile phones to patients—contribute to higher smoking cessation rates.

Secondary objectives include: (1) comparing smoking cessation rates to other user metrics and technical aspects of the system; (2) investigating the relationship between usage of the app used in the 3M4Chan intervention [35] and users’ opinions of messages; and (3) determining if a relation exists between the users’ physical activity levels and their mobile app usage, and their smoking cessation rates.

Both the primary objective and the secondary objectives are common for the clinical and public pilots, although their methodologies and assessments do not completely coincide.

The present document shows the protocol version 1.0.4, 30 May 2018. Major protocol amendments, if any, will be handled by the Taipei Medical University informing any involved stakeholder, and updating the ClinicalTrials.gov registry diligently. Table 1 describes the clincal and public pilot. We followed the Standard Protocol Items: Recommendations for Intervention trials (SPIRIT) guidelines while writing this protocol manuscript (see Additional file 1).

**Table 1 Tab1:** Description of the clinical and public pilot

Name of the pilot	Number of patients	Groups	Treatment	Data to be assessed
Clinical pilot (RCT; 100 patients)	50	Control	Usual care (behavioral therapy and pharmacological treatment)	Smoking cessation rate (clinically validated)
	50	Intervention	Usual care + 3M4Chan app (advanced tailored messages)	Smoking cessation rate (clinically validated)
				Recommender system
				User engagement
				Physical activity
Public pilot (RCT; 1000 patients)	500	Control	m-health (basic tailored messages)	Smoking cessation rate (self-reported)
				Recommender system
				User engagement
				Physical activity
	500	Intervention	m-health (advanced tailored messages)	Smoking cessation rate (self-reported)
				Recommender system
				User engagement
				Physical activity

*RCT* randomized controlled trial

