### Materials

The clinical pilot will make use of all the materials normally used to treat patients at the smoking cessation units at Taipei Welcome Clinic and Taipei Medical University Hospital.

Carbon monoxide levels will be tested using a PiCO Smokerlyzer CO-oximeter; a value range of 0–6 will be considered normal for a non-smoker. Similarly, a Safecare Biotech COT Rapid Test device, which contains line indicators for positive and negative test results, will be used to measure urinary cotinine levels.

Several smoking cessation medications will be used during the trial: Nicotinell TTS 20 and TTS 30 patches, Nicotinell 2-mg chewing gum and 10-mg inhalers, Buporin 150-mg sustained-release tablets, and Champix 0.5-mg and 1-mg tablets. The dosage and duration of each medication will be prescribed by the physician, and the patients will be charged NT$200 per consultation.

In addition, our specially designed mobile app will be used to deliver motivational health messages. Figure 3 shows its interface in both English and Mandarin. The app has been programmed in Android’s native language. It uses Mirth Connect as its communication channel [39], Firebase for platform notifications, and PostgreSQL as its database management system.

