**Fig. 3 Fig3:**
[figure not shown]
Screenshots of the app (English and Mandarin versions) showing different sections

A nurse will provide patients with instructions for downloading and using the app. Questions related to the patient’s basic demographic information and an extended profile (including social influences, plan of action, skills, attitudes, and self-efficacy with regard to smoking) will be assessed in the app.

The data obtained from the database will be analyzed in a comma-separated value (CSV) format using SPSS software.

Users’ physical activity data will be collected using their mobile phones. The mobile app will use GoogleFit [40] to track daily physical activity. These data will be available to users through the GoogleFit app but not displayed within the 3M4Chan app, as it will be utilized for research purposes only.

Patients will be followed up after 60, 120, and 180 days of their initial consultation with a variance margin of 5 days. In the initial consultation, the patient will be assessed in the smoking cessation unit after they have been referred from either the pneumology unit or another clinical department. Smoking-related symptoms, treatment adherence, daily cigarette use, and possible adverse events will be discussed and exhaled carbon monoxide, urinary cotinine, and other clinical information, such as weight and height, will be assessed. Quality of life (EQ-5D-5 L, IPAQ, and SF-36) questionnaires will also be collected. The patient will be instructed on relaxation techniques and on tips to avoid smoking.

During the second consultation, physicians will gather patient information on smoking-related symptoms, treatment adherence, daily cigarette use, possible adverse events, exhaled carbon monoxide and urinary cotinine levels, and other clinical information. Coaching for relapse prevention will be performed.

At the third consultation, information about smoking-related symptoms, treatment adherence, possible adverse events, exhaled carbon monoxide and urinary cotinine levels, and other clinical information will again be collected. New relaxation techniques will be explained if the previously taught techniques have not been effective. Techniques for relapse prevention will be reviewed. It will also be collected the users’ physical and psychological health state, their exhaled carbon monoxide levels, the results from a urinary cotinine test, and will be asked clinical information such as weight and height.

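### The clinical pilot is labelled single-blinded with blinded outcome assessors, but the protocol does not deliver that blinding and partly disclaims it

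*Protocol article*

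**What the plan says.** The section on protection against other sources of bias states: "The clinical pilot component of this study is designed to be a single-blinded randomized control trial". Of the care providers it says that "they will be responsible for patient allocation", and it defends their position on the ground that they have no competing interest: "we think it is unlikely they influence any group by the lack of blinding". It then says of both pilots: "In both cases, outcome assessors will be blinded although the different variables in the datasets will determine the groups". Non-clinical researchers who take no part in delivering the intervention are to assess the results.

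Table 1 gives the clinical intervention arm as "Usual care + 3M4Chan app (advanced tailored messages" and the control arm as usual care. For the clinical control arm it lists only the smoking cessation rate. For the clinical intervention arm it adds recommender system, user engagement and physical activity data.

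Under Materials, the cotinine device "contains line indicators for positive and negative test results". The visit descriptions there include "During the second consultation, physicians will gather patient information on smoking-related symptoms, treatment adherence, daily cigarette use, possible adverse events, exhaled carbon monoxide" (the sentence goes on to urinary cotinine) and, at the fourth consultation, "as well as a questionnaire assessing the satisfaction about the motivational messages received through the 3M4Chan app".

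**The concern.** A single-blind label tells the reader that one party does not know the allocation, and a claim of blinded assessment tells them that the outcome was determined without that knowledge. The sentence on assessors makes the claim and takes it back in its second half. If no party in the clinical pilot is shown to be masked, the label is wrong, and the trial report would carry it forward.

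What is at stake is mainly the credibility of a small comparison (50 per arm), where a few classifications can change the result. The argument from competing interests does not restore the blinding: expectation can influence care or a reading without any financial or professional interest.

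**Working it through.** The point is textual, so each role in the clinical pilot is traced through the protocol article.

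1. **Patients.** The planned-interventions section and Table 1 give control usual care and intervention usual care plus the app. No sham app is described. Patients know their arm.
2. **Care providers.** They are responsible for allocation, and the protocol concedes that they are not blinded. Under Materials, a nurse instructs patients on the app. Not blind.
3. **Those who obtain the primary outcome.** Physicians are named as gathering CO and cotinine at the second consultation, and the data-management section has physicians enter the clinical data in the health record. No masked reader is described. For the initial and third consultations the person is not named. The fourth-consultation list does not mention these two tests, although the measures section needs them at day 180.
4. **Those who assess the results.** They are independent of delivery, which is not the same as masked. The protocol says that the dataset variables determine the group. Table 1 shows how this can happen: app, engagement and activity data exist in one clinical arm only, so their presence identifies the arm.

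No role is shown to be blind.

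**How much room for bias is left.** The statistical analysis section fixes most of the classification: CO of 0 to 6 counts as non-smoker, and any discrepancy between the tests counts as smoker. A favourably read cotinine strip therefore changes a patient's status only if CO is also 0 to 6. Missing data are less settled. The statistical analysis section carries the last observation forward, while the sample-size section treats non-return at month 6 as failure. A patient abstinent at day 120 and absent at day 180 is a non-smoker under the first rule and a failure under the second. Reconciling the two is a separate matter, but it is a choice that should be made before the arm is visible.

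**Hypothetical illustration.** The document gives no misclassification rate, so everything here except n = 50 per arm and the two-sided 0.05 level is assumed. Let the true non-smoker rate be p in both arms, and let k patients in one arm be wrongly classified as non-smokers on average. The observed rates are then p and p + k/50, with mean m, and each such patient moves that arm by 1/50 = 2 points. With

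- s0 = √(2·m(1 − m)/50), the standard error used by the test,
- s1 = √([p(1 − p) + (p + k/50)(1 − p − k/50)]/50), the actual standard error,

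the rejection rate is P(Z > (1.96·s0 − k/50)/s1) + P(Z < (−1.96·s0 − k/50)/s1).

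- p = 0.30, k = 3: s0 = 0.0940, s1 = 0.0939, limits 1.325 and −2.603, giving 0.0926 + 0.0046 = 0.097.
- p = 0.30, k = 5: s0 = 0.0954, s1 = 0.0949, limits 0.917 and −3.025, giving 0.1796 + 0.0012 = 0.181.
- At the two planning rates in the sample-size section, k = 3 gives 0.109 (p = 0.20) and 0.092 (p = 0.50), and k = 5 gives 0.210 and 0.170.

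So k = 3 gives about 9% to 11% and k = 5 about 17% to 21%, against a nominal 5%. These figures show sensitivity. They do not estimate what happened in this trial.

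**The case against.** The strongest reply is that the outcome is biochemical and rule-based. CO is a number set against a fixed cut-off, cotinine is a positive or negative test, and discordance counts against abstinence, so little discretion is left. The protocol is also open about the providers' lack of blinding. The data-management section keeps clinical data in the health record and app data in a separate database, so smoker status could be derived without any app variable, and whether a coded file is used is the kind of detail that an article may leave out.

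Most of this stands as a limit on size. It does not make the blinding statement true: no masked person is identified, and the protocol's own remark about the datasets points the other way. Nor do outcome rules protect against performance bias, or against bias in the patient-reported EQ-5D-5L, SF-36 and IPAQ.

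Several stronger readings are tempting but not supported:

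- **Unblinded staff decide how discordant pairs are scored.** They do not; the rule is written down.
- **The analysts certainly see the arm while classifying patients.** This is an inference from the concession and Table 1, not a stated fact.
- **The same physicians take the tests at every visit.** They are named for these tests at the second consultation only.
- **The two professionals who check entered data could serve as masked readers at the visit.** Nothing says that they attend visits or are unaware of the arm, so this would be a new staff role.
- **The public pilot has the same fault.** Table 1 lists the same data for both public arms and both use the app, so the presence of data does not reveal the arm there.

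**Conclusion.** The point holds for the clinical pilot. The label and the claim of assessor blinding are wrong as written: patients and care providers are unblinded, the physicians named for the second-visit tests are not described as masked, and the results assessors are independent but not shown to be masked. Confidence is high for patients and providers, and lower for the analysts, whose unblinding is inferred.

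The resulting bias cannot be sized from the document. The false-positive figures rest on invented numbers of misclassified patients and on an assumed common true rate, and they should not be quoted as a property of this trial. The outcome rules keep the likely effect on the primary result below what an unblinded subjective endpoint would allow.

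**What to change.** 1. Describe the clinical pilot as open-label for patients and care providers, and drop the single-blind label.
2. Make the assessor blinding real. Give the non-clinical researchers a clinical-pilot primary-outcome file that holds only study number, coded arm, visit, and the CO and cotinine results. Lock smoker/non-smoker status, the handling of missing data and the primary analysis on that file. Merge the app, GoogleFit and satisfaction data only afterwards, and say so in the section on bias.

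The cost is a wording change and one extra data-export step, which the separate storage of clinical and app data should make easy. It can still be done while the trial is recruiting, since it touches the analysis files and not the visits. The downsides are small: the single-blind label is lost, and the readings taken at the visits themselves remain unmasked, which the report should acknowledge.
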